### Blinding

The patients, surgeons, anesthetists, data collectors, and outcome assessors are all blinded. Only the data manager and the specific study coordinator are unblinded to the group allocation. Unblinding by the investigator for a given patient will occur only if the knowledge of treatment assignment will materially change the planned management of a medical emergency. Investigators will have direct access to a given patient’s individual study treatment and the decision to unblind a patient’s treatment assignment in an emergency situation resides with the investigator; however, the investigator should attempt to contact the medical monitor or appropriate study personnel to discuss options before unblinding the patient’s treatment assignment unless the urgency of the medical situation precludes this.

### Interventions

Patients will be randomized to receive 0.2 mg/kg dexamethasone or saline placebo, administered as an intravenous bolus within 5 min after induction of anesthesia. All other aspects of perioperative management will follow the regular protocols in our institution, as detailed in another trial protocol [23]. Non-trial glucocorticoids were prohibited for up to 7 days after surgery.

### Primary outcome measures

The primary endpoint is the Comprehensive Complication Index (CCI) score within 30 days after the operation. The CCI takes into account all cumulative complications and receives values between 0 and 100 (Table 1) [24]. The CCI’s weight of complication (wC) is based on the established Clavien-Dindo classification [25]. Detail calculation was presented below.

**Table 1 Tab1:** The comprehensive complication index calculation

**Grade**	**wC**	**CCI single value**
Grade I	300	8.7
Grade II	1750	20.9
Grade III		
Grade IIIa	2750	26.2
Grade IIIb	4550	33.7
Grade IV		
Grade IVa	7200	42.4
Grade IVb	8550	46.2

Clavien-Dindo grade V always results in CCI 100

$$CCI=\sqrt{wC1+wC2\dots +wCx}/2$$; the online CCI calculator is available at www.assessurgery.com

*wC*, weight of complication; *CCI*, the Comprehensive Complication Index

### Secondary outcomes measures

The secondary endpoints are listed as follows:The incidence of major complications (Clavien-Dindo≥3), 30 daysThe incidence of postoperative pancreatic fistula (ISGPS classification), 30 daysThe incidence of post-pancreatectomy acute pancreatitis (ISGPS classification), 30 daysThe incidence of infection (including wound infection and intra-abdominal abscess), 30 daysThe incidence of relaparotomy, 30 daysPostoperative length of stayMortality, 30 daysMortality, 90 days

### Tertiary outcomes measures

The tertiary endpoints are listed as follows:Serum CRP value on POD1 and POD 2Average blood glucose levels on POD 1 and POD 2Lymphocyte and neutrophil levels on POD 1 and POD 2Overall medical costs

### Data collection and follow-up

All data will be collected after the patients provide informed consent. Patients will be followed according to normal postoperative routine in our institution. There is no extra outpatient clinic visit outside normal routine follow-up. All relevant factors will be recorded on a trial electronic case report form (eCRF). The schedule of enrolment, interventions, and assessments is shown in Table 2.

**Table 2 Tab2:** Schedule for enrollment, interventions, and assessment

**Timepoint****	**Study period**					
	**Enrolment**	**Allocation**	**Post-allocation**			**Close-out**
	***Preoperative*** ***visit*** ***-t***	***0***	***POD 0*** ***t1***	***POD 1*** ***t2***	***POD 2*** ***t3***	***POD 30*** ***tx***
**Enrolment:**						
**Eligibility screen**	X					
**Informed consent**	X					
**Allocation**		X				
**Interventions:**						
***Dexamethasone***			X			
***Saline placebo***			X			
**Assessments:**						
***Intraoperative outcomes***			X			
***Blood tests***				X	X	
***Primary/secondary outcomes***						X

*POD* Postoperative day

### Data management and monitor

In this study, the Guancui EDC system will be used for data collection. Patient data will be documented by dedicated trial personnel and managed in the eCRF. Data will be entered through a dedicated WeChat applet or web browser input masks. All staff involved in the data collection process are to be qualified to access the research database. Data collection must be collected in accordance with standard specification processes. The system cannot automatically identify the data needed to enter through manual input by the data entry person. All study-related information and participant information will be stored securely at the study site with locked cabinets in areas with limited access. The database will be secured with a password-protected access system.

An independent Data and Safety Monitoring Committee (DSMC) will be appointed to evaluate the study safety parameters. The DSMC will exist of two independent statisticians and two independent surgeons. DSMC members will meet before trial initiation, 3 months after the inclusion of the first patient, thereafter every 6 months, and after the interim analysis. All adverse events will be recorded on the eCRF. If the DSMC identify safety issues, they will have the prerogative to request unblinded outcomes. The safety of this trial will be evaluated in standardized intervals by the appointed institutional ethics and DSMC, which will advise regarding the trial’s status. More specifically, 30-day mortality will be monitored independently in each arm, and if a safety threshold of 5% is reached at any given time, the trial will be withheld for further safety evaluation and potential decision for early termination.

### Statistical analysis

#### Sample size calculation

The Finland RCT reported that perioperative hydrocortisone significantly reduced postoperative complications after PD in high-risk patients (18% vs. 41%; *P* < 0.05; Clavien-Dindo III-IV) [14]. Based on the pancreatic transection line frozen samples, high-risk patients with >40% acini consisted of more than half of the cohort. Because 0.2 mg/kg dexamethasone has theoretically a similar anti-inflammatory effect to hydrocortisone, so we presume that the perioperative dexamethasone could reduce at least 30% of major complications in the whole PD cohort.

For the sample size calculation, a 30% reduction in the rate of overall complications was assumed with a power of 80% (*β*=0·2), and an α-error of 0.05. This yielded an estimated group size of 128 patients. Finally, the sample size of this study is based on the primary outcome — CCI. Because CCI is more sensitive and requires a smaller sample size compared to the Clavien-Dindo classification in RCT, 128 patients in each group are sufficient for the primary outcomes [24]. Finally, the target recruitment of the PANDEX trial will be set at 300 to account for 20% dropout or deviation of the protocol. Thus, 150 patients are required in each group.

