#### General analysis principle

Normality will be examined using the Shapiro-Wilk test. For normal distribution, continuous variables will be described as mean and standard deviation (SD) and compared using the *t*-test. For non-normal distribution, continuous variables will be described as medians and interquartile range (IQR) and compared using the Mann-Whitney test. test. Categorical variables will be expressed as frequencies and percentages and compared using chi-squared test or Fisher exact test when appropriate. We have no imputation plans for missing data. All statistical tests will be tested with two sides, *P* < 0.05 is considered to represent a statistically significant difference, with a CI of 95%. All analyses were performed using Stata (Stata Corporation, version 15, College Station, TX, USA).

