#### Efficacy analysis

All outcomes will be analyzed using modified intention-to-treat analyses, where all randomized patients who undergo scheduled pancreaticoduodenectomy were included in the analyses. Criteria to remove patients from analyses after randomization are as follows:Scheduled pancreaticoduodenectomy was not performed (e.g., disseminated cancer, enucleation).Total pancreatectomy was performed.Additional hepatic resection.Patient withdrew consent prior to surgery.

The primary outcome is a sum of all complications that are weighted for their severity, based on the Clavien-Dindo classification, the Comprehensive Complication Index (CCI). CCI score will be presented as mean ± SD and in case of skewed distributions as median and range. Values will be compared by the *t*-test or the Mann-Whitney test as appropriate.

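### The 80% power behind 128 per group belongs to a binary rate of overall complications; power for the primary CCI comparison has not been established

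*Protocol article*

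**What the plan says.** Under Primary outcome measures: "The primary endpoint is the Comprehensive Complication Index (CCI) score within 30 days after the operation". This is a score from 0 to 100. Under Efficacy analysis: "Values will be compared by the *t*-test or the Mann-Whitney test as appropriate".

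The Sample size calculation section then makes three moves.

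1. *Rationale.* It cites a hydrocortisone trial in high-risk patients (18% vs 41%, Clavien-Dindo III-IV) and infers: "we presume that the perioperative dexamethasone could reduce at least 30% of major complications in the whole PD cohort".
2. *Calculation.* It changes endpoint: "a 30% reduction in the rate of overall complications was assumed with a power of 80" per cent and "an α-error of 0.05". The result is 128 per group. No control rate is printed.
3. *Transfer.* It says that the sample size rests on the CCI, and justifies this with: "Because CCI is more sensitive and requires a smaller sample size compared to the Clavien-Dindo classification in RCT, 128 patients in each group are sufficient".

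The General analysis principle section fixes sidedness: "All statistical tests will be tested with two sides". No CCI mean, difference or SD appears anywhere in the article.

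**The concern.** Three endpoints are used as if they were interchangeable: major complications for the rationale, overall complications for the arithmetic, and CCI for the conclusion. The 80% attaches only to the second. That endpoint is not the primary outcome and is not in the list of secondary outcomes, which names major complications instead.

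The statement that the size rests on CCI therefore conflicts with the calculation printed just before it. What carries the 80% across is a general remark about the sensitivity of CCI, with no check for this trial.

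At stake is how a neutral result will be read. It would be reported as coming from a trial with 80% power for its primary endpoint, when nobody has said what CCI difference the trial could detect.

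**Working it through.** **Inputs from the article.** Two-sided alpha 0.05 (z = 1.960), power 80% (z = 0.842), 1:1 allocation, 128 per group, a 30% reduction, and the CCI weights in Table 1. The only event rates given are 41% and 18%. **Assumed, because not given:** the overall-complication control rate, the CCI SD and the severity mix.

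**Step 1. Reproduce 128.** Read 30% as relative, so p2 = 0.7 × p1. With pooled variance,

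n = [1.960 √(2p̄(1−p̄)) + 0.842 √(p1(1−p1) + p2(1−p2))]² / (p1−p2)².

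At p1 = 0.581, p2 = 0.4067 and p̄ = 0.49385: n = (1.386 + 0.586)² / 0.1743² = 3.889 / 0.03038 = 128.

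With unpooled variance, n = 7.849 × [p1(1−p1) + p2(1−p2)] / (p1−p2)². At p1 = 0.575 and p2 = 0.4025: 7.849 × 0.4849 / 0.02976 = 128.

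So 128 implies a control rate of about 58% (about 61% with continuity correction). An absolute reduction of 30 points would need only 27-43 per group at control rates of 35-80%, so the relative reading is the one that fits. The calculation is coherent for overall complications once that rate is supplied.

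**Step 2. Try the rates the article does print.**
- 41% vs 18% taken directly: 58 (unpooled) to 61 (pooled) per group.
- 41% reduced by 30% to 28.7%: 7.849 × (0.2419 + 0.2046) / 0.123² = 232 per group unpooled, 235 pooled. Power at 128: z = (0.123 × √128 − 1.960 × √(2 × 0.3485 × 0.6515)) / √0.4465 = 0.106, so power = Φ(0.106) = 54%.

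Neither gives 128. The number does not come from the endpoint used to argue for the 30%.

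**Step 3. What 128 per group delivers for a mean CCI difference.** Detectable d = (1.960 + 0.842) × √(2/128) = 2.802 × 0.125 = 0.35. For Mann-Whitney under normality, 0.35 / √0.955 = 0.36.

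| Assumed CCI SD | Detectable difference (0.35 × SD) | Power for an assumed 5-point difference |
|---|---|---|
| 15 | 5.3 | 76% |
| 20 | 7.0 | 52% |
| 25 | 8.8 | 36% |

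For an assumed 8-point difference at SD 20, power is 89%.

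**Step 4. Does CCI inherit the 80%?** CCI was simulated from the Table 1 weights with 58% of control and 40.6% of treated patients having any complication, 128 per group, and several assumed grade mixes. One of them was 25/40/18/8/6/3% for grades I, II, IIIa, IIIb, IVa and IVb, with no grade V.

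| Scenario | Mann-Whitney | t-test |
|---|---|---|
| One complication per affected patient, severity unchanged | 73-77% | 51-67% |
| Poisson number of complications with reduced rate, grade mix unchanged | 84-86% | 82-84% |
| As above, with severity also reduced | 89-90% | 90-91% |

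Chi-squared power for the binary endpoint was 81-82% in the same kind of run. In the first row, severity adds noise but no signal, so CCI does worse than the binary test. In the other rows the treatment also changes the number or grade of complications, and CCI does better. The direction depends on how the drug works.

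**The case against.** It can fairly be said that the binary calculation is a loose but recognisable conservative bound. CCI sums all complications and weights them, so it should gain when a drug lowers their number or severity. The plan presumes at least 30% fewer major complications, which makes unchanged severity a pessimistic reading of its own premise. The second and third simulation rows bear this out. A neutral result would also be judged from the CCI difference and its confidence interval, and no analysis, test or patient count is wrong. All of that stands, and it limits the point.

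Three stronger readings are tempting, and the document supports none of them.

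- *The trial is underpowered for CCI.* That follows only in the first scenario, and the mixes and SDs are assumptions. A standardised difference of 0.35 may or may not be realistic.
- *The missing control rate is itself an error.* A journal article may leave that figure to the full protocol, so its absence alone is no finding.
- *The plan claims 80% power for major complications.* It does not. The 54% in step 2 describes a secondary endpoint at a rate quoted for high-risk patients. It shows why the wording needs reconciling and breaks no promise.

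What this does not answer is the text itself: the size is said to rest on CCI, and no CCI quantity was used. The article cites a source for the general remark on sensitivity, but a general remark cannot fix the power of this trial.

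**Conclusion.** The point holds in limited form. The 80% power belongs to a 30% relative reduction in overall complications from an implied control rate of about 58%. It is not power for the t-test or Mann-Whitney comparison of CCI, and the sentence carrying it across is unsupported. Under the plan's own implied effect, simulated CCI power lies between about 51% and 91%, depending on the test and on assumptions about the number and severity of complications. CCI power is therefore not established, which is different from being shown to be low. The endpoint switch stands in the published text and does not depend on any document not shown.

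**What to change.** Keep N, and change the sample-size text in three places.

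1. Replace the sentence declaring 128 sufficient with: 128 evaluable patients per group give 80% power (two-sided 5%) for a standardised CCI difference of about 0.35. Convert this to CCI points with the blinded pooled SD of patients already recruited (120 at submission, according to Trial status). Until then, show 5.3, 7.0 and 8.8 points for assumed SDs of 15, 20 and 25.
2. Attach the 80% power for a 30% reduction to overall complications only, with the control rate behind it.
3. Reconcile the rationale (major complications) with the calculation (overall complications). Note that a 30% reduction from the only quoted major-complication control rate, 41% in high-risk patients, would have about 54% power at 128 per group.

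The cost is rewording and one blinded SD estimate, with no new patients and no change to the analysis. The downside is that the stated power claim becomes less favourable.

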### Randomization

After enrollment, randomization and allocation will be done on the day of surgery. The randomization will be centralized in the Guancui EDC system. We applied a randomized block design with a block number of six in a 1:1 ratio. A data manager who is independent of the data analysis or patient enrolment will generate the randomization schedule at the beginning of this trial. After providing informed consent, patients who are consistent with the inclusion and exclusion criteria will be randomly assigned to the treatment group or the control group. The randomization schedule will not be available to study recruiters or physicians. The allocation is only available for the independent data manager and the specific study coordinators in the Guancui EDC system. Specifically, when appropriate patients are enrolled, the researcher will inform the data manager, and then the random number and exact treatment group will be returned simultaneously.

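### The target of 300 covers a loss of at most 14.7% from 128 per group, not the 20% that the sample size section states

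*Protocol article*

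**What the plan says.** All the figures are in the Sample size calculation section of the protocol article. The calculation assumes that "a 30% reduction in the rate of overall complications was assumed", "with a power of 80% (*β*=0·2), and an α-error of 0.05". Its result is given as "This yielded an estimated group size of 128 patients". The section then turns to the primary outcome, the Comprehensive Complication Index (CCI). It argues that this score needs fewer patients than the Clavien-Dindo classification, so that "128 patients in each group are sufficient for the primary outcomes". The last step adds the allowance for loss: "the target recruitment of the PANDEX trial will be set at 300 to account for 20% dropout or deviation of the protocol". It concludes: "Thus, 150 patients are required in each group".

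Three other sections determine which patients drop out of the analysis:

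- Efficacy analysis defines a modified intention-to-treat set. It removes randomised patients for four reasons: the scheduled operation was not done, a total pancreatectomy was done, a liver resection was added, or consent was withdrawn before surgery.
- Participant enrollment and withdrawal says that the information of a patient who withdraws is not recorded.
- General analysis principle says that missing data will not be imputed.

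**The concern.** An allowance for loss should leave the required number once the stated loss has occurred. Here 128, 20% and 150 stand in the same section, and on a first check 150 less 20% falls below 128. If so, the published justification promises a margin that the target does not provide. At the plan's own loss rate, the analysed number would be smaller than the number the section calls required.

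The losses would reduce the analysed number directly, because patients removed or withdrawn are not analysed and missing scores are not imputed. The 20% also combines two things, dropout and deviation from the protocol. Only some deviations lead to removal under the modified intention-to-treat rule, so it is unclear what the 20% is meant to cover.

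**Working it through.** **Inputs**

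- Required size per group: 128, so 256 in total (Sample size calculation).
- Stated allowance: 20% (same section).
- Target: 300 in total, 150 per group (same section).
- Allocation: 1:1 (Randomization: "We applied a randomized block design with a block number of six in a 1:1 ratio").
- Power 80% and alpha 0.05 (Sample size calculation), two-sided (General analysis principle: "All statistical tests will be tested with two sides").

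**Step 1. Can 150 per group be reproduced?**

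- Dividing by the retained fraction, n/(1 - d): 128/0.80 = 160 per group, 320 in total.
- The common shortcut, n x (1 + d): 128 x 1.2 = 153.6, so 154 per group, 308 in total.

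Neither gives 150. The shortcut applied to the total, 256 x 1.2 = 307.2, and then rounded down may explain the 300, but this is a guess. As it stands, 150 is 150/128 - 1 = 17.2% above 128.

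**Step 2. What remains after a 20% loss?**

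150 x 0.80 = 120 per group, 240 in total. The shortfall is 128 - 120 = 8 per group, 16 in total.

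**Step 3. What loss does 150 per group cover?**

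1 - 128/150 = 22/150 = 14.7%. That is 22 patients per group, 44 in total.

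**Step 4. What would the shortfall cost in power?**

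Take whatever effect gives 80% power at 128 per group. In the normal approximation its noncentrality at that size is 1.960 + 0.842 = 2.802. Noncentrality scales with the square root of the group size:

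- At 120 per group: 2.802 x sqrt(120/128) = 2.802 x 0.968 = 2.713.
- Power: Phi(2.713 - 1.960) = Phi(0.753) = 0.774.

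Power falls from 80% to about 77%, a loss of about 2.6 percentage points. No control rate is needed for this.

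**Step 5. Cross-check with two proportions**

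The section states no control rate, so one has to be assumed. With a relative reduction of 30%, a two-sided test and no continuity correction, the size per group would be:

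| Assumed control rate | n per group |
|---|---|
| 50% | 170 |
| 55% | 143 |
| 58% | 129 |
| 60% | 120 |

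The 58% rate comes closest to 128. Under it, power is 79.9% at 128 per group and 77.3% at 120, which agrees with step 4. Steps 1 to 3 do not depend on this assumption.

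**The case against.** The arithmetic is hard to dispute, and no other section corrects it. The case on the other side concerns what follows from it.

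A reader might infer that the trial loses its 80% power for the primary outcome if 20% are lost. The article does not support that. It derives 128 from a complication rate and presents it as more than enough for the CCI. If that argument is accepted, 120 per group could still give 80% power for the CCI. Whether the argument is well founded is a separate matter. This objection stands, so the 77% is conditional on 128 being exactly the size that gives 80%.

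A reader might also take 120 per group as the number to expect. It is a worst case. The 20% counts deviations as well as dropout, and patients whose deviation is not among the four listed reasons stay in the modified intention-to-treat set. One example is a patient given a prohibited non-trial glucocorticoid. The article does not split the 20%, so the true loss may be smaller. This also stands.

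Finally, it is tempting to say that deviation has no place in the allowance and should be deleted. That rests on one reading of an undefined term. Three of the four listed removals concern an operation that differed from the one planned, and these can fairly be called deviations. The term needs aligning, not deleting.

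None of this makes 150 per group cover a 20% loss from 128.

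**Conclusion.** The statement is wrong as written. From a required 128 per group, a target of 150 per group covers a loss of at most 14.7%, whereas 20% would need 160 per group (320 in total). This rests only on the section's own 128, 20% and 150.

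The severity is minor. In the worst case the shortfall is 8 analysed patients per group and about 2.6 points of power. That worst case assumes that all of the 20% is lost from the primary analysis and that 128 is exactly the size for 80% power. If losses stay at or below 14.7%, the required 128 is met. The finding does not show that the trial is underpowered for the CCI.

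**What to change.** Keep the target of 300 and restate what it allows for. Suggested wording:

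*The target of 300 (150 per group) allows for up to about 14.7% of randomised patients not contributing to the primary analysis, through the exclusions listed under Efficacy analysis, withdrawal, or a missing 30-day CCI. If 20% were lost, 120 per group would remain, and power would be about 77% for the effect that gives 80% at 128 per group.*

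Naming withdrawal and missing scores matters, because both reduce the analysed number and go beyond the four listed exclusions.

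In the same edit, align the reference to protocol deviation with the reasons under Efficacy analysis, and say that patients with other deviations remain in the modified intention-to-treat set.

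The cost is two or three sentences. Recruitment, design and analysis do not change, and the stated margin becomes slightly less favourable. If the sponsor wants a true 20% margin, the target would have to be 320, which is 20 more patients. A shortfall this small does not require that.
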